### Outcome measures

Data are collected from professionals (OTs, managers, and physicians) and client-caregiver couples. Data from professionals are gathered at baseline (T_0_), 6 months (T_1_), and 12 months (T_2_) (Table 1). Information from client-caregiver couples is collected at baseline (T_0_), 3 months (T_1_), 6 months (T_2_), 9 months (T_3_), and 12 months (T_4_) (Table 2).

**Table 1 T1:** Overview of outcome measures on professional level

Variable	PO	SO	EE	BG	Instrument/Source	T0	T1	T2
Demographics				✓	Survey	✓		
Adherence	✓		✓		Vignettes & CAQ	✓	✓	✓
Use of Community OT	✓							
Strategy costs	✓		✓		Costs registered by SPs Costs survey OTs, MGs, MDs		✓	✓
Referral rate		✓			Collection of referrals*		✓	✓
OT knowledge		✓			Knowledge questionnaire	✓	✓	✓
MG knowledge		✓			Knowledge questionnaire	✓	✓	✓
MD knowledge		✓			Knowledge questionnaire	✓	✓	✓

PO = primary outcome; SO = secondary outcome; EE = economic evaluation; BG = background; T0 = baseline measure; T1 = 6 month follow-up measure; T2 = 12 month follow-up measure; CAQ = COTiD Adherence Questionnaire; SPs = strategy providers; OTs = occupational therapists; MGs = managers; MDs = medical doctors * Referrals are collected in the one year period between T0 and T2

**Table 2 T2:** Overview of client-caregiver outcome measures

Variable	SO	EE	BG	Instrument	T0	T1	T2	T3	T4
**Client**									
Demographics			✓	Survey	✓				
Depression			✓	GDS	✓				
Mental State			✓	MMSE	✓				
Quality of life	✓			Dqol	✓		✓		✓
Quality of life	✓	✓		EQ-5D	✓		✓		✓
Execution of daily activities	✓			AMPS	✓		✓		✓
Problems in daily life	✓			COPM	✓		✓		✓

**Caregiver**									
Demographics			✓	Survey	✓				
Quality of Life	✓			Dqol	✓		✓		✓
Quality of life	✓	✓		EQ-5D	✓		✓		✓
Clients execution of daily activities	✓			IDDD	✓		✓		✓
Sense of competence	✓			SCQ	✓		✓		✓
Problems in daily life	✓			COPM	✓		✓		✓
Depression			✓	CES-D	✓		✓		✓
Healthcare costs	✓	✓		RUD lite basic	✓				
Healthcare costs	✓	✓		RUD lite follow-up		✓	✓	✓	✓

SO = secondary outcome; EE = economic evaluation; BG = background; T0 = baseline measure; T1 = 3-month follow-up measure; T2 = 6-month follow-up measure; T3 = 9 -month follow-up measure; T4 = 12-month follow-up measure; GDS = Geriatric Depression Scale; MMSE = Mini Mental State Exam; Dqol = Dementia Quality of Life Scale; AMPS = Assessment of Motor and Processing Skills; EQ-5 D = EuroQol 5D; COPM = Canadian Occupational Performance Measure; IDDD = Interview for Deterioration of Daily Activities in Dementia; SCQ = Sense of Competence Questionnaire; CES-D = Center for Epidemiologic Studies Depression Scale; RUD Lite basic = Resource Utilisation in Dementia - Baseline questionnaire; RUD Lite follow-up = Resource Utilisation in Dementia - follow-up questionnaire

#### Primary outcome measures

Use of community OT is defined as the number of clients with dementia referred to community OT according to the COTiD program (either specific or non-specific) compared to the total number of referrals of people with dementia to community OT services. Specific referrals are those in which the name of the program is mentioned (e.g. OT according to the COTiD program). Non-specific referrals contain a referral question in which the physicians requests evaluation, therapy, or advice concerning daily activities in the home environment of the client and/or caregiver. Referrals concerning only advice regarding an aid (singular questions) are only included in the total number of referrals collected.

Data on referrals are collected by requesting participating OTs from each cluster to send copies of all referrals concerning community OT for people with dementia and/or their caregiver to the research team.

Adherence of OTs to the COTiD program is defined as 'the degree to which OTs intent to treat clients with dementia and their caregivers according to the COTiD program'. The use of Standardized Patients (SP) can be seen as the golden standard to measure adherence [17], however, this is a costly method. Closed ended questionnaires are commonly used to gather data, but are likely to evoke socially desirable answers. In addition, respondents tend to overestimate their behavior. Therefore, we will use vignettes, which seems a more valid method compared to questionnaires and more feasible than SPs. Vignettes are simulations of realistic events used to obtain participants' knowledge, attitudes, or opinions on how they would behave in a theoretical situation [18]. Previous studies [17,19] showed that vignettes provide sufficiently valid data to measure adherence. In addition, they were found to be sensitive to variation in setting [17] and suitable for creating a sufficient case-mix [17,20].

Two vignettes were created and reviewed by an expert panel. Open-ended questions are used to avoid overestimation of adherence due to cues in the questions [21]. The same questions were used for both vignettes. All questions are based on quality indicators that are based on the COTiD program and defined by experts and consensus rounds of OT's ([name], [name], [name], [name], [name], [name]: Quality Indicators for Community Occupational Therapy for People with Dementia and their Caregivers: Development and Testing, in preparation).

In order to evaluate change in adherence over time and change between research-groups, data gained through the vignettes are quantified using a standardized scoring system. This system will assist in producing an adherence percentage between 0% (no adherence) and 100% (complete adherence). The content of the scoring system is based on quality indicators and was reviewed by an expert panel. Inter-rater reliability of the scoring system will be evaluated prior to data analysis.

As the use of vignettes is fairly new an additional close-ended questionnaire is developed to gather data on adherence to the COTiD program. The questionnaire contains questions on the frequency OTs perform different activities. OTs are asked to rate the frequency of these activities on a five-point scale from "never" to "always". Data gathered through this questionnaire as well as data provided by the web-based system will be used for validation purposes.

Both the vignettes and the close-ended questionnaire were formatted in an electronic survey system. Participants were provided with a personal link through e-mail to get access to these questionnaires.

#### Secondary outcome measures on professional level

Healthcare professionals' knowledge about the COTiD program is measured using a close-ended electronic questionnaire. The focus of each questionnaire is adapted to the knowledge required for each group of professionals (OTs, managers, and physicians). The questionnaires were evaluated by an expert panel.

#### Secondary outcome measures on client-caregiver level

To evaluate the effect of the CI-strategy on client-caregiver couples, treatment outcomes are measured. Table 2 shows which information is collected. Demographic information collected concerns age, marital status, education, (previous) profession, disease, disabilities, and relationship between client and caregiver. Data collection takes place at the client and/or caregivers home environment.

### Sample size and power calculations

We developed a cluster randomized trial, with randomization at institute level. Adherence of OTs to the COTiD program and the use of community OT are both primary endpoints. We hypothesize that the experimental intervention will increase OTs' adherence to the COTiD program from 20% to 50% and increase the use of community OT from 5% to 25%. Per institute, two OTs are included and on average at least 10 clients are expected to be eligible for community OT. The Intra cluster Correlation Coefficient (ICC) of OT within institutes (with respect to adherence) and the ICC of clients within institutes (with respect to OT use) is assumed to be 0.05. Corrected for the clustering of OTs within institutes, the 'effective' sample size of each cluster (institute) with respect to adherence is 1.9 OTs (= n/[1+(n-1)*ICC], where n is the number of OTs per institute (i.e. 2) and ICC is the intra cluster correlation of OTs within an institute (i.e. 0.05)). Corrected for clustering of clients within institutes, the effective sample size of clusters with respect to community OT use is 6.8 clients (n = 10, ICC = 0.05). Therefore, randomizing 30 clusters to control and 15 to intervention provides the same power for adherence as an individually randomized trial of 57 (= 30 × 1.9) subjects on control versus 29 (= 15 × 1.9) subjects on intervention, where the subjects are independent (not correlated within clusters). Thus, this cluster randomized trial provides 80% power to detect an increase from 20% to 50% in adherence. Similarly, this trial provides the same power for use of community OT as an individually randomized trial of 204 (= 30 × 6.8) subjects on control and 102 subjects on intervention. Thus, this cluster randomized trial provides 99% power to detect an increase from 5% to 25% in community OT use. The combined power for both endpoints then is at least 0.8*0.99 = 79% [22].

### Informed consent and ethical approval

In the Netherlands studies involving human subjects need to undergo a medical ethics review if they are subject to the Medical Research Involving Human Subjects Act (WMO). Studies involving completing questionnaires do not generally bring a study within the scope of this Act. To be sure the research team did submit materials to the Human Subjects Committee of the region Nijmegen/Arnhem. This committee decided that the questionnaires in our study were not too burdensome for participants including the people with dementia and their caregivers. Therefore, the study was exempt from further review by the Human Subjects Committee.

All participants were requested to sign a consent form prior to data collection. Professionals and client-caregiver couples are participating voluntarily and can stop participation at any time.

### Statistical methods

Random effects regression models will be used to evaluate differences in adherence and in use of community OT between the experimental and control group. Baseline scores will be used as covariates and type of setting and OT will be used as random factors.

Differences in knowledge between professionals (occupational therapists, physicians, and managers) in the experimental and control group will be evaluated using t-tests, unless data have a substantially skew distribution in which case non-parametric tests are used. Random effect regression models for repeated measures will be used to evaluate differences in knowledge at different times of measurement within each group and between groups. The influence of several characteristics of the professionals on their knowledge level will be evaluated using ANOVA (e.g. sex) and linear regression (e.g. age, years of professional experience).

Random effects regression models will be used for analyses of covariance of the outcome measures (AMPS process [23], IDDD performance [24], DQOL [25], SCQ [26], EQ-5 D [27] at 6 and 12 months (see Table 2)) based on an intention-to-treat analysis of all available data. Treatment differences between baseline and 6 months and baseline and 12 months will be computed by analysis of covariance, with age, sex, relation to patient, and baseline scores on the co-morbidity, MMSE scores, GDS scores, and outcome variable at baseline as covariates.

For all tests significance will be tested using two-sided tests with an alpha level of.05.

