## Methods/Design

### Trial Design

A single blinded, cluster randomized controlled design is used to compare the effectiveness and cost-effectiveness of the two implementation strategies. An independent statistician stratified the clusters by type of setting (hospital, nursing home, and mental health services) and randomized them to either the control (educational strategy) or experimental group (the combined implementation strategy) (see Figure 1). Clusters were randomized using a 2 to 1 (control vs. experimental) ratio, as it is expected that physicians in the experimental group will refer more clients for this community occupational therapy intervention than those in the control group. This assumption implies that more clusters are needed in the control group to collect data from a sufficient number of client-caregiver couples. At the time of randomization 45 organizations agreed to participate in the study.

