### Participants

#### Healthcare professionals

A cluster consists of occupational therapists, managers, and physicians working at a healthcare setting which delivers community occupational therapy (outpatient service general hospital, outpatient treatment from nursing home & outpatient community mental health services). Clusters were preferably formed out of professionals working at the same organization. However, in several cases professionals from different organizations formed a cluster as these were the usual networks in current clinical practice. Clusters were approached between January and December of 2009 and asked to participate in the study.

Eligibility criteria for clusters:

1. Clusters consist of at least two OTs, one physician, and one manager

2. Outpatient occupational therapy treatment is provided by the cluster

3. Each cluster is able to include at least 8 client-caregiver couples in the study

4. OTs within a cluster completed the post-graduate course on the COTiD program before the start of the study.

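### The primary-outcome model leaves out the institute, the unit that was randomised, so its tests run above the stated 5%: about 5.6% for adherence and about 7.5% for use of community OT

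*Protocol article*

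**What the plan says.** The sample size section of the protocol article states the unit of randomisation: "We developed a cluster randomized trial, with randomization at institute level". It gives the cluster sizes, "Per institute, two OTs are included and on average at least 10 clients are expected to be eligible for community OT", assumes an ICC of 0.05 within institutes for both endpoints, and converts 30 control and 15 intervention clusters into effective sample sizes.

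The Trial Design section says what type of setting means: "An independent statistician stratified the clusters by type of setting (hospital, nursing home, and mental health services"). It is the randomisation stratum, with three levels. The eligibility criteria for clusters add "Clusters consist of at least two OTs, one physician, and one manager".

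The Statistical methods section covers both primary outcomes in two sentences: "Random effects regression models will be used to evaluate differences in adherence and in use of community OT between the experimental and control group", followed by "Baseline scores will be used as covariates and type of setting and OT will be used as random factors". Neither that section nor any other gives an institute effect, a robust variance or a cluster-level analysis for the primary comparisons.

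**The concern.** In a cluster randomised trial the error variance of the treatment contrast must include the variation between randomised units. Here the named random factors sit above the institute (setting) and below it (OT), and the institute itself is missing. Every institute holds at least two OTs in the same arm. An OT effect captures correlation among observations from one OT, but it counts the two OTs of an institute as two independent pieces of evidence on the strategy. The sample size section assumes that they are not.

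The gap matters more for use of community OT. That outcome is a share of referrals. Physicians make the referrals, and the strategy tries to raise them through contacts with the cluster's physicians and managers, so dependence across the whole cluster is to be expected. If the institute variance is left out, standard errors are too small and a primary test exceeds its stated alpha.

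**Working it through.** **Inputs.** From the sample size section: 30 control and 15 intervention clusters, 2 OTs and 10 clients per institute, ICC 0.05, adherence 20% versus 50%, use 5% versus 25%. From Statistical methods: two-sided alpha 0.05, random factors setting and OT.

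**Step 1. The plan's own power.** Effective cluster size is n/[1 + (n − 1) × ICC].
- Adherence: 2/1.05 = 1.905, given as 1.9. Then 30 × 1.9 = 57 and 15 × 1.9 = 28.5, taken as 29.
- Use: 10/1.45 = 6.897, given as 6.8. Then 30 × 6.8 = 204 and 15 × 6.8 = 102.

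A two-sided comparison of two proportions gives 80.1% (unpooled variance) to 81.3% (pooled) for adherence, against 80% stated. For use it gives 99.3% to 99.7%, against 99% stated. The plan's figures reproduce, and they already carry the institute design effect.

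**Step 2. Type I error when the institute effect is left out.** Let R be the true variance of the treatment contrast divided by the variance the model assumes. Then type I error = 2 × [1 − Φ(1.96/√R)].

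*Adherence.* With two OTs treated as independent, R = 1 + (2 − 1) × 0.05 = 1.05. 1.96/√1.05 = 1.913, which gives **5.6%**.

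*Use of community OT, OT factor fitted.* Two assumptions are not in the documents: the 10 clients split 5 and 5 between two OTs, and all correlation lies at institute level. The correlation of the two OT means is then 0.05/(0.05 + 0.95/5) = 0.05/0.24 = 0.208, so R = 1.208. 1.96/√1.208 = 1.783, which gives **7.5%**.

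*Use, upper bound.* If the OT factor absorbs none of the clustering, R = 1 + (10 − 1) × 0.05 = 1.45. 1.96/√1.45 = 1.628, which gives **10.4%**.

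**Step 3. Sensitivity to ICC and cluster size.** The ICCs other than 0.05 below are assumptions.

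| ICC | Adherence | Use, OT fitted | Use, nothing absorbed |
|---|---|---|---|
| 0.01 | 5.1% | 5.6% | 6.1% |
| 0.05 (plan) | 5.6% | 7.5% | 10.4% |
| 0.20 | 7.4% | 11.6% | 24.2% |

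The plan expects an average of 10 clients or more. With 20 referrals per institute (an assumption) and the OT factor fitted, R = (0.05 + 0.95/20)/(0.025 + 0.95/20) = 0.0975/0.0725 = 1.345, which gives 9.1%.

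**Step 4. Simulation.** Set-up: 45 clusters, 15 per stratum, allocated 2:1, two OTs each, normal outcome, 4,000 replicates. The Monte Carlo standard error near 5% is √(0.05 × 0.95/4000) = 0.34 points. The model with random setting and independent OTs rejected in 5.5% to 5.6% of replicates for adherence and 7.7% for use at ICC 0.05. Analysis at institute level with fixed setting gave 5.0% to 5.1% in the same scenarios. Replacing random by fixed setting, still without the institute, left the rejection rate the same in most scenarios (5.6% and 5.6%; 7.7% and 7.7%) and within 0.2 points otherwise.

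**The case against.** The strongest defence is that the plan does not ignore clustering. It fits an OT factor, OTs send in the referral copies, and each OT's adherence is measured three times, so OT is a genuine grouping in both data sets. That stands: the OT factor is insufficient on its own, but it is not wrong. It also means that 10.4% is a bound and not the expected error.

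A second defence is that an article may leave model details to a fuller plan. That would excuse silence. Here the article names its random factors, and they do not match its unit of randomisation or its sample size section.

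A third is that use of community OT might be analysed as one proportion per cluster, which would remove the inflation. An OT random factor would then have no role, so the sentence would still need correcting.

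A reader might infer three stronger points, and the documents support none of them:
- That treating setting as random is part of the cause. Three levels estimate a variance badly, and a stratifier belongs in the fixed part, but the simulation shows that this choice does not itself shrink the standard errors.
- That the error is well above 10%. Such values need a model with no clustering term, larger clusters than the 10 used in the calculation, or a higher ICC.
- That the client-caregiver models share the fault. The article says only that they are random effects models and names no factors, so they contain no stated error.

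**Conclusion.** Wrong as written. The stated model for both primary outcomes omits the randomised unit. At the plan's ICC of 0.05 the consequence is very small for adherence (about 5.6% against 5%) and material for use of community OT (about 7.5%). The second figure rests on an even split of 10 clients between two OTs and on all correlation being at institute level. It grows with more than 10 referrals per institute, and the whole excess vanishes if the institute ICC is zero, which the plan does not assume. The stated power is not in question.

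**What to change.** In Statistical methods, replace the sentence on random factors so that the primary-outcome models have:
- a random intercept for institute (cluster);
- OT nested within institute for the repeated adherence scores;
- type of setting as a fixed stratification covariate, which is good practice with three levels and separate from the inflation;
- inference based on the 45 clusters, with a small-sample correction suited to the model type. Kenward-Roger degrees of freedom suit a linear mixed model for adherence but do not carry over directly to a referral proportion. There a cluster-level analysis with 45 − 4 = 41 degrees of freedom (arm plus three settings) is one option.

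The change is one sentence and needs no new data. Relative to the model as written, standard errors at the plan's ICC grow by √1.05 = 1.02 for adherence and √1.208 = 1.10 for use. The planned power has already paid for this. The only cost not yet counted is the small-sample reference value, 2.02 in place of 1.96 at 41 degrees of freedom. Put into the Step 1 calculation, it leaves adherence at 78.4% to 79.7% and use above 99%.

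### Knowledge is compared between arms with t-tests or rank tests that ignore institute and T0, beside a mixed model that names no institute effect and is not said to lead

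*Protocol article*

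**What the plan says.** Knowledge of OTs, physicians and managers is a secondary outcome. Table 1 of the Protocol article schedules it at T0, T1 and T2 for all three professions.

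Statistical methods gives two analyses for it, in consecutive sentences:

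- The first sentence says that the contrast of the two arms "will be evaluated using t-tests, unless data have a substantially skew distribution in which case non-parametric tests are used".
- The second sentence plans a model for the repeated scores: "Random effect regression models for repeated measures will be used to evaluate differences in knowledge at different times of measurement". It applies that model both inside each arm and to the contrast of the arms.

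The section closes with a general rule: "For all tests significance will be tested using two-sided tests with an alpha level of.05".

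On the design, Sample size and power calculations states: "We developed a cluster randomized trial, with randomization at institute level". The eligibility criteria under Healthcare professionals say: "Clusters consist of at least two OTs, one physician, and one manager". For the two primary outcomes that are modelled, adherence and use of community OT, Statistical methods plans random-effects regression with baseline scores as covariates.

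**The concern.** A two-sample t-test or rank test takes every person as an independent observation. OTs of one institute share an arm and a workplace, and the protocol itself expects their results to be correlated: its power calculation discounts each pair of OTs for clustering. Testing knowledge in the same OTs without that discount understates the standard error. Neither test has a term for T0, although T0 is collected and is used as a covariate for the primary outcomes.

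The second sentence does not settle the matter. It covers the same between-group contrast with a repeated-measures model, but names no institute effect, and nothing says which result is the one to report. A random effect for the person handles repeated scores within a person. It does not handle two OTs within one institute. At stake are a type I error above the nominal 5% for the OT comparison, some avoidable loss of precision in all three professions, and two candidate p-values for one hypothesis.

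**Working it through.** **Inputs from the Protocol article**

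- Clusters: "randomizing 30 clusters to control and 15 to intervention provides the same power for adherence" as a stated individually randomised trial (Sample size and power calculations).
- OTs per institute: 2 in the power calculation. The eligibility criteria set 2 as the minimum.
- Physicians and managers per cluster: minimum 1 of each.
- ICC: "the ICC of clients within institutes (with respect to OT use) is assumed to be 0.05", and the same sentence gives the same value to OTs with respect to adherence. No ICC is given for knowledge.
- Alpha: 0.05, two-sided.

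**Assumptions made here**

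- The ICC of 0.05 carries over to knowledge. The range 0.10 to 0.30 is illustrative.
- The correlation r between T0 and follow-up knowledge is 0.5 to 0.7. The article gives none.

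**Step 1. Reproduce the plan's own figure.** The article states no figure for knowledge, so the check is on adherence. The effective number of OTs per institute is 2/[1 + (2 − 1) × 0.05] = 2/1.05 = 1.905, stated as 1.9. That gives 30 × 1.9 = 57 and 15 × 1.9 = 28.5, stated as 29. Power for 20% against 50% with 57 and 29 is 81.3% (pooled variance) or 80.1% (unpooled), against the stated 80%. The figure reproduces, and it rests on the clustering correction that the knowledge test omits.

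**Step 2. Type I error of the uncorrected test for OTs.** With m people per cluster, the design effect is DE = 1 + (m − 1) × ICC, and the true two-sided error is 2 × [1 − Φ(1.96/√DE)]. For m = 2:

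| ICC | DE | √DE | True type I error |
|---|---|---|---|
| 0.05 (article's value) | 1.05 | 1.025 | 5.6% |
| 0.10 (assumed) | 1.10 | 1.049 | 6.2% |
| 0.20 (assumed) | 1.20 | 1.095 | 7.4% |
| 0.30 (assumed) | 1.30 | 1.140 | 8.6% |

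Simulation with 30 and 15 clusters of two at ICC 0.05 gave 5.7% for the t-test (20,000 runs) and 5.7% for the rank test (5,000 runs). Moving to a rank test for skewed data therefore does not remove the problem.

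**Step 3. Physicians and managers.** At m = 1, DE = 1.00 and the error stays at 5.0%. There is no inflation.

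**Step 4. Precision lost by leaving out T0.** With score variance σ², the variance is σ² for a test on follow-up scores alone, 2(1 − r)σ² for a test on change scores, and (1 − r²)σ² with T0 as a covariate.

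- Against follow-up scores alone, the covariate cuts variance by r²: 25% at r = 0.5 and 49% at r = 0.7.
- Against change scores, it cuts variance by (1 − r)/2: 25% at r = 0.5 and 15% at r = 0.7.

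The article does not say which score or time point enters the t-test, so both comparisons are shown.

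**The case against.** The strongest reply is that the adjacent sentence already plans a random-effects model for knowledge between groups, with T0 among the repeated measures. If that model is the one reported, T0 is used and most or all of the precision loss disappears. The two sentences may also be meant for different purposes, a simple comparison of arms and a study of change over time, and an analysis plan that is not shown could rank them. This stands in part: it would be wrong to say that the plan makes no use of T0 for knowledge. It does not remove the point. The t-test is a stated between-arm analysis, the model is also stated to be between groups, the article ranks neither, and the model names no institute effect.

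The second reply is size. At the article's own ICC with two OTs per cluster, the excess is about 0.6 percentage points on a secondary outcome. That stands.

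A reader might infer something stronger: that errors are understated for all three professions, that the error approaches 10%, or that ignoring T0 is like discarding a third or more of the sample. The documents do not support these readings. The minimum of one physician and one manager gives no inflation, and no larger number is stated. An error of 9.8% needs three OTs per cluster and an ICC of 0.20 (DE = 1.40), neither of which the article gives. The gain equivalent to 33% to 96% more professionals (1/0.75 − 1 and 1/0.51 − 1) needs the assumed correlations, a test on follow-up scores alone, and that test being the one reported.

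**Conclusion.** The point holds as a specification error of modest size in the analysis of a secondary outcome. As written, the t-test or rank test is the wrong between-arm test for OTs, because it ignores a correlation that the protocol assumes elsewhere for the same people. The true type I error is about 5.6% with two OTs per cluster at ICC 0.05, and about 6.2% to 8.6% if the ICC for knowledge were 0.10 to 0.30. The first figure rests on carrying the adherence ICC over to knowledge, and the others on an assumed range. For physicians and managers at one per cluster, the only cost is possible imprecision, and only if the unadjusted test is reported. Independently of these numbers, the plan gives two between-group analyses of one outcome without saying which leads, and the better of the two does not name institute.

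**What to change.** Drop the t-test and rank-test sentence as the between-arm comparison, and make the mixed model already planned the single between-arm analysis of knowledge, one model per profession:

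- T1 and T2 scores as outcomes, with the T0 score as a covariate. T0 should not also be an outcome time in the same model, since it would then be used twice.
- Setting as a covariate, because randomisation was stratified by it.
- A random intercept for person.
- A random intercept for institute wherever a profession has more than one member per cluster, so always for OTs. With one physician or manager per cluster, institute and person are the same unit and the two intercepts cannot be separated, so the person intercept is enough.
- If scores are clearly skewed, a bootstrap interval that resamples whole institutes within arm. With 15 institutes in the smaller arm it is approximate.

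The cost is a change of analysis wording and a little more analysis work, with no new data. Allowing for clustering widens the OT interval slightly: by about 2.5% at ICC 0.05 with two per cluster (√1.05 = 1.025), before any gain from T0.
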